## 9. QUALITY CONTROL AND QUALITY ASSURANCE

CAPRISA has a long track record of conducting quality research. This study will be monitored by the CAPRISA Quality Assurance Team, which will include 6-monthly reports on study conduct findings. Particular attention will be placed on consent forms, adherence to the protocol, completion of source documents and CRFs, and appropriate and timely communication with the ethics committee, especially in the case of any protocol deviation. In addition, the study team will have weekly meetings to monitor study progress. CAPRISA routinely measure QC and retention rates on all studies.

## 10. ETHICAL CONSIDERATIONS

Collection and analyses of socio-demographic information, reproductive history, sexual risk taking behaviors, and biological samples taken for clinical purposes will be covered by ethics approval. No investigational products will be utilized in this study and hence there is no requirement for regulatory approval from the South African Medicines Control Council. IRB

approval will be sought from the University of KwaZulu-Natal (UKZN) Biomedical Research Ethics Committee (BREC) (FWA00000678). Informed consent will be obtained from potential participants to participate in the study and to store genital and blood samples to test for STIs and genital tract cytokines collected at screening and follow-up visits. These biological specimens will be handled by trained staff and labeled with a unique identifier for each participant. The results will be transmitted to the clinics in an electronic format but only accessed by authorized and trained clinic staff. Only key members of the data team will have access to the electronic data, which will be password protected. Once enrolled into the study participants will be able to withdraw at any point. This will not have a detrimental impact on their care by the study team at the PCZ CDC and CAPRISA clinics.

## 11. EXPECTED RESULTS AND ALTERNATIVE APPROACHES

We expect to find an overall decline in cytokine levels after treatment in the participants. In addition, we expect to recruit sufficient participants to study the effect of enhanced STI treatment with each of the STIs. Even if we are unable to demonstrate a reduction in cytokine levels, the data generated for the study will provide valuable information about cytokines and STIs and this will be useful in generating hypotheses for new studies. In addition, we will have information that will allow us to evaluate the use of GeneXpert for STI detection and expedited partner therapy in a high prevalence, low resource setting.

## 12. POTENTIAL ROADBLOCKS

A potential challenge could be the implementation of **expedited partner therapy**. Participant concerns may include compromising confidentiality, difficulties broaching the subject with sexual partners, and concerns that this could provoke partner violence or the partner may leave. In order to address these concerns and develop culturally appropriate processes, we will conduct a series of focus groups with potential recruits and staff members coordinated by a skilled facilitator. Follow-up focus groups with participants will assess whether our approach has increased any potential risks for these women.

Other potential challenges include: 1) **Loss to follow-up**: In order to improve participant compliance and follow up, all participants will be counselled by the research nurse and will have mobile phone access to the clinic staff. In addition, we have accounted for this in our sample size calculations. 2) **Anxiety about the use of the Softcup**: This will be minimised through counselling and advice about Softcup insertion. We have evaluated the Softcup for specimen collection and it was preferred by 100% of participants compared to the speculum examination. 3) **Allergies to therapy**: We will be using widely used medications that have a low allergenic potential and are recommended by the most recent South African STI Management Guidelines. 4) **Pregnancy during follow up**: Participants will be counselled about safer sex and the use of contraception and, if found to be pregnant, will be referred to antenatal care.

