### **d) Follow-up with Test of Cure**

All participants will be contacted after one week, to check for any adverse effects from the treatment and to establish if sexual partners were contacted and took the treatment. Participants will be offered the opportunity to talk to a counsellor or nurse if required. Participants will be asked to reattend for a test of cure and a repeat cytokine test after six weeks. The GeneXpert detects the organism's DNA, which may persist for several weeks after treatment. If the participant is cured and not reinfected, then the test should be negative at six weeks [70]. Participants will all be asked to report to the clinic at three months for cytokine tests and repeat STI and HIV screen. If a participant tests positive for an STI they

will be retreated after checking results on the visits and NG resistance from the previous visit. In the event of a positive HIV result, participants will be assessed and managed according to the South African Adult HIV management guidelines [71], but will be encouraged to complete follow-up in the study.

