#### **Feasibility and acceptability among patients, their partners and staff of EPT intervention**

Cure rate at six weeks and 3 months will be compared between those women who participate in and deliver EPT in the study, and those who do not. In addition, qualitative research will include focus group discussions before and after the EPT intervention. Initial group discussions will focus on potential barriers of patient delivered partner therapy and strategies women think may work to navigate around these barriers. After implementation the focus groups discussions will focus on participants' experiences of partner notification, whether it increased any experience of risk (e.g. violence or abandonment) and what women would want if they were to do this again. Every effort will be made to invite partners of the index cases, either to attend to the clinic, or to be contacted by phone to discuss their experiences of this intervention. Finally, staff will also have the opportunity to share their experiences.

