### 6.1 Potential risks and adequate protection against risks

Although the proposed activities pose minimal risks to participants, confidentiality will continue to be a priority and will be protected. This includes, storing all data forms in secure lockers after entry into an encrypted database with controlled access, stored data will be password protected, and program staff will be trained on research ethics. In addition, all participant interviews, focus group discussion, and surveys will take place in privacy and in appropriate locations. A unique identification system will be used to protect participant information, and at no time will the participant identifiers be shared with non-program staff. Participants who become pregnant will be referred to appropriate ante-natal care

programmes. Most importantly, any individual who wishes not to participate in research will still be able to access all of the program services without any issue.

All data generated by this project will be shared via peer-reviewed publications in a timely fashion. To protect individual patients, no identifying information will be used and reports and publication will include only summary statistics.

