## **8. ANALYSIS**

Demographic and baseline behavioral characteristics will be described. Cytokine concentrations will be log transformed to ensure normality. Paired t-tests will be performed comparing cytokine concentrations before and after STI treatment, i.e. baseline compared to 6 weeks. Additional analysis will be performed comparing the 12 week follow-up time point to the baseline and 6 week measurements. Paired t-tests will be performed for each STI and BV and any STI, comparing baseline cytokine measurements with that measured at 6 and 12 weeks, and general linear models will be used to adjust for other STIs the participants may have. The false discovery rate method will be used to correct for multiple comparisons. In addition, longitudinal multivariate modelling approaches, which accommodate the correlation between cytokine concentrations, will be used to assess the changes in cytokine concentrations over time [73]. Data will be analyzed using SAS version 9.3 (SAS Institute Inc., Cary) and R.

The accuracy of GeneXpert STI testing will be assessed using sensitivity and specificity measures compared to the standard multiplex PCR assay for CT/NG/TV and Mycoplasma genitalium that is being used in other CAPRISA studies.

The feasibility and acceptability of GeneXpert will be determined through the administration of questionnaires to staff and participants. The quantitative variables measured in the questionnaire will be summarized and mean outcomes will be compared using t-tests, while medians will be compared using the Wilcoxon rank sum test. Categorical variables will be compared using Fisher's exact test.

When determining cure rates, the date of cure will be estimated as the midpoint between the last positive STI test date and the first negative STI test date. The focus group discussions

will be analysed for emerging themes in order to determine the feasibility and acceptability of expedited partner therapy interventions.

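### Partner violence and abandonment after expedited partner therapy are to be assessed only in focus groups; no individual question is specified, so affected women can be missed and their number cannot be reported

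*Protocol*

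**What the plan says.** Section 12 of the protocol treats EPT as a possible difficulty. Alongside confidentiality and the difficulty of raising the subject, it lists "concerns that this could provoke partner violence or the partner may leave". It then names the way this will be checked: "Follow-up focus groups with participants will assess whether our approach has increased any potential risks for these women".

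The paragraph on EPT feasibility and acceptability under Section 5.5.3 (secondary study outcomes) gives the same method. The groups held after implementation will explore how women found telling their partners, including "whether it increased any experience of risk (e.g. violence or abandonment) and what women would want if they were to do this again". Section 8 says that the discussions "will be analysed for emerging themes in order to determine the feasibility and acceptability of expedited partner therapy interventions".

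Every followed woman is also contacted individually. Section 5.5.1 d) gives the purpose of the one-week contact: "to check for any adverse effects from the treatment and to establish if sexual partners were contacted and took the treatment". It adds: "Participants will be offered the opportunity to talk to a counsellor or nurse if required". Section 5.4 describes the interviewer-administered questionnaire as covering sexual behaviour and general and reproductive health. The schedule of evaluation repeats a behavioural risk questionnaire at 6 weeks and 3 months.

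Section 6.1 opens: "Although the proposed activities pose minimal risks to participants, confidentiality will continue to be a priority and will be protected". It goes on to data protection, privacy of interviews and referral in pregnancy. It does not mention partner violence or abandonment.

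**The concern.** The protocol foresees a specific harm from one component of its intervention and assigns its detection to a method that need not reach every exposed woman. Focus groups explain experience well. They do not establish who was harmed or how many, because the protocol does not say that all EPT recipients attend, disclosure takes place in front of others, and the output is a set of themes.

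Two things are at stake. The first is safety information: a woman who met a violent reaction after taking the first pack home need not be identified through any contact the protocol describes, although the schedule provides for EPT again at 6 weeks and 3 months. The second is the secondary objective on EPT feasibility and acceptability: the study could describe what some women said but not how many of those given packs were affected. Silence in a group could also be taken as evidence of no harm.

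This is not a detail left to an analysis plan. The protocol itself chooses the method of assessment.

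**Working it through.** **1. Which contacts could pick up the harm?**

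- Focus groups after implementation (Sections 5.5.3 and 12): violence and abandonment are a stated topic. Size and selection are not given, and the analysis is thematic (Section 8). They give no numerator and no denominator.
- One-week contact (Section 5.5.1 d): reaches all followed women. The listed items are adverse effects of treatment and whether partners were reached and took it. It asks whether the pack was delivered, not what followed.
- Offer of a counsellor or nurse at one week: made if required, so it relies on the woman speaking up.
- Questionnaire at entry, 6 weeks and 3 months (Section 5.4 and the schedule): no item on partner reaction is described.
- Scheduled counselling at each contact: labelled as STI and safe-sex counselling.
- Phone number in the partner pack (Section 5.5.1 c): described as a service for the partner.
- Mobile phone access to clinic staff (Section 12): offered to support follow-up; again the woman must raise the harm.

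Only the first names the harm, and it is the only one not stated to reach every woman.

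**2. The denominator.** Packs go to participants with NG, CT or TV (Section 5.5.1 c). The only fixed count is 32 CT-positive women (Section 8). Table 4 gives 28, 32 and 427 in the row for correlation 0.60, and this reproduces. With SD equal to the baseline mean and a 50% reduction, the standardised difference is 0.5 / √(2 × (1 − 0.6)) = 0.5 / 0.894 = 0.559. A paired t-test at 80% power and two-sided α = 0.05 (sidedness is assumed) needs 27.1, so 28 pairs. Then 28 / 0.9 = 31.1, so 32, and 32 / 0.075 = 426.7, so 427. The total number of EPT recipients is not stated, because women with NG and a sub-sample with TV come on top and co-infections overlap.

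**3. How easily can groups miss affected women?** Assume 32 recipients, 2 of them affected, and random attendance of k women. The probability that neither attends is C(30, k) / C(32, k):

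- k = 8: (24 × 23) / (32 × 31) = 552 / 992 = 0.56
- k = 16: (16 × 15) / 992 = 240 / 992 = 0.24
- k = 24: (8 × 7) / 992 = 56 / 992 = 0.06

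On average the groups would leave out 1 − k/32 of the affected women: 75%, 50% and 25%. The values of k and the 2 affected women are assumptions; the protocol gives neither. Attendance is no guarantee of disclosure, so these are chances of having an affected woman in the room, not of learning about her.

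**4. What would individual questions give?** Exact (Clopper-Pearson) two-sided 95% intervals; for zero events the upper limit is 1 − 0.025^(1/n):

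- 0 of 32: 0 to 10.9%
- 1 of 32: 0.1 to 16.2%
- 3 of 32: 2.0 to 25.0%
- 0 of 29 (about 10% of 32 lost: 32 × 0.9 = 28.8): 0 to 11.9%
- 0 of 64 and 0 of 100 (assumed totals): 0 to 5.6% and 0 to 3.6%

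These are wide, but each is a reportable figure, which the present plan cannot produce.

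**The case against.** The strongest reply is that the method looks deliberate and is not the only protection. Focus groups are held before implementation, and Section 5.5.1 c) allows EPT to be adapted in their light, for example with a helpline or notification by a counsellor. Section 13 places the focus-group work under an expert in qualitative research on gender-based violence. Women are counselled at every contact and can phone staff. The objective in Section 4.2 is to explore feasibility and acceptability, and no harm rate is promised. With no comparator arm, a count could not show that EPT raised the risk.

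Much of this stands. The study should not be faulted for failing to estimate a causal increase, and the safeguards make it less likely that harm goes wholly unnoticed. But they prevent harm, or wait for the woman to report it. None of them is a question put to each exposed woman, and expert supervision of focus groups does not turn them into individual ascertainment.

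A reader might infer more than the text supports:

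- That women are never asked about violence. The questionnaire's items are not shown; one can say only that no such question is specified.
- That harmed women will be missed. They can be; some may volunteer the information.
- That violence is the main harm of EPT. Section 12 lists it among several concerns without ranking them.
- That harmed women are the least likely to attend. This is plausible, but the protocol offers nothing on it, so the calculation uses random attendance.
- That a harmed woman would simply receive another pack. A further pack follows a new positive NG, CT or TV test, at a visit that includes counselling and the questionnaire.
- That a maximum number of EPT recipients follows from Section 8. The NG and TV prevalences there are lower limits, and TV is sub-sampled.

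**Conclusion.** The point holds as a gap in ascertainment. For a risk the protocol itself names, the sole stated assessment is a thematic analysis of groups of unstated size; no individual contact as described asks about it, and the risk section omits it. Harm can go unidentified, and the number affected among women given packs cannot be reported.

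The size cannot be fixed from the protocol. Under the assumption of 2 affected among 32 and random attendance, the chance that the groups contain neither runs from 0.06 (24 attending) to 0.56 (8 attending). The primary cytokine analysis is unaffected. What is affected is safety information on EPT and the secondary objective on its acceptability. The conclusion rests on the questionnaire as the protocol describes it; if the instrument already holds a partner-reaction item, the remaining task is to state it in the protocol and report it.

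**What to change.** Add to Sections 5.5.1 d) and 5.5.3 that every woman given a partner pack is asked, individually and in private, a short fixed set of questions on her partner's reaction: threats, violence, coercion and abandonment linked to the pack. Use the one-week call and the 6-week and 3-month questionnaires.

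Record positive answers as social harms, with the offer of the counsellor or nurse already provided for in Section 5.5.1 d). In Section 8, state that the number of women reporting each type of harm will be given over the number given packs, with the number who answered and an exact 95% confidence interval. Describe the result as a frequency, not as an increase caused by EPT. Keep the focus groups to explain what happened and why, and add this risk to Section 6.1.

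The cost is a few questions at existing contacts and a short amendment, with no new visit. Contacts become slightly longer, and phone calls need a check that the woman can speak privately. One limit remains: no contact is scheduled after a pack given at 3 months, so reactions to those packs would not be captured, and the report should say so.

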## 13. FEASIBILITY

Participants will be recruited from the STI clinic situated at the PCZ Communicable Disease Centre, which is located in central Durban in the transport hub for public commuters by rail, bus or minibus taxis. Annually, approximately 40 000 cases of STIs are diagnosed syndromically and treated at this clinic. The clinic has the added advantage of housing a laboratory which facilitates rapid sample processing, and on site microscopy. The CAPRISA eThekweni research facility is adjacent to the clinic. CAPRISA has a vast experience in recruiting and retaining participants for clinical studies with a highly trained staff of doctors, nurses, counsellors and pharmacists. Investigation of genital cytokines by Luminex multiplex assays have long been conducted as part of a collaboration between CAPRISA and the

University of Cape Town (UCT) [1, 2, 48, 49]. The CAPRISA Mucosal Immunology Laboratory now conducts genital cytokine assessments in-house, as it is equipped with both a Bio-Plex 200 and a Mag-Pix array reader, and several post-doctoral researchers and technicians trained by UCT and international collaborators to conduct reliable and reproducible assessments of cytokine concentrations. The group at John Hopkins has over 30 years of experience evaluating and implementing new STI diagnostic methods and are currently involved in a project to determine ideal characteristics of STI point-of-care tests. Finally, [name] from Health Economics and HIV and AIDS Research Division (HEARD) at the University of KwaZulu-Natal is one of the leading international experts in qualitative research on gender-based violence in South Africa, and will be supervising the focus group work on EPT.

#### 14. RELEVANCE

This proof of concept study will determine whether a reduction in inflammatory cytokines can be achieved by adopting a novel strategy of enhanced STI management in a group of women at high risk of HIV. This is particularly relevant in KZN which is at the epicentre of the HIV epidemic. The proposed STI management will include a package of highly innovative interventions, which, if successfully implemented, could lead the way for South Africa to transition to a more effective, diagnostic care model for STIs leading to a reduction in HIV incidence.

